## Abstract

**Background:**

Novel coronavirus disease 2019 (COVID-19) has been the subject of a numerous research projects over the past year. In cases with a severe disease course or threatening long-term impairment due to disease, the German health care system offers insured persons the possibility of medical rehabilitation. In contrast to what was observed and expected at the beginning of the pandemic, COVID-19 patients with varying degrees of disease severity are represented in rehabilitation. To date, there is no common consensus on the content and aftercare of rehabilitation nor is there any knowledge about the short- and long-term effects of such a rehabilitation programme. In addition, these aspects were not considered with regard to the varying severity of the course of the disease. The present research project investigates this question.

**Methods:**

The study sample will consist of *N* = 350 rehabilitants after COVID-19 and a comparison group (CG) with *N* = 230 rehabilitants suffering from an obstructive respiratory disease. The participants will be recruited at five German rehabilitation facilities and undergo medical rehabilitation. This prospective, exploratory, multicentre, mixed-methods study will be evaluated as follows: (A) The quantitative portion includes questionnaires at different points in time (at the beginning and end of rehabilitation, after six and twelve months) and contains standardised measurement instruments. For example, participation limitations, quality of life, health status, fatigue, psychomental limitations and disorders, performance in different areas of life and ability to work are measured. (B) Qualitative interviews are held at different times (end of rehabilitation, after six and twelve months), and an expert workshop is conducted. Topics are rehabilitation content, satisfaction and aftercare as well as different outcomes on subjective health and participation impairments.

**Discussion:**

Studies on other indications have already shown that pneumological rehabilitation has positive effects. Thus, it is expected that an improvement in different dimensions will be observed at the end of rehabilitation in both groups. With regard to the different severities of COVID-19, this study evaluates the long-term developments. Subsequently, the authors will elaborate concrete recommendations for medical rehabilitation after different courses of disease with regard to existing pneumological rehabilitation concepts.

**Trial Registration:**

German Register of Clinical Trials, www.drks.de.Identifier: DRKS00023642; Registered: 01.12.2020.Date and version identifier: 08.04.2021; version 4.

## Background

COVID-19 is caused by the SARS-CoV-2 virus and is characterised by an unspecific, varying and diverse course of the disease, ranging from the lack of symptoms to severe pneumonia with lung failure and death [1]. The majority of patients have a mild to moderate course of disease (approximately 81 %) [2]. As a result, approximately 18 % were hospitalised in the first wave of the disease [3]. However, a moderate course of COVID-19 does not equate to a fast recovery. Patients with a severe course of the disease or those who have long-lasting symptoms require further treatment [4].

There are currently no uniform definitions of the long-term effects of COVID-19 (“long COVID”) [1]. Especially in very mild or asymptomatic courses, little is known to date. The Robert Koch Institute (RKI) refers to studies of SARS-CoV-1 infection to obtain information about the long-term consequences of COVID-19. According to this information, long-term physical and psychological consequences could be expected for COVID-19 patients. RKI refers to studies that report persistent impairment of lung function [5, 6], reduced physical performance [5, 6], reduced health-related quality of life [5, 7] and various mental and neuropsychiatric impairments, such as anxiety disorders, panic attacks, depression, post-traumatic stress disorder [7]. Such evidence for COVID-19 survivors is currently only found in a few studies with short- to medium-term follow-up. In an Italian study, 143 hospitalised COVID-19 patients were questioned 60 days after their first symptoms. Only 13 % of the respondents stated that they were completely symptom free. In contrast, 32 % reported one or two symptoms, and 55 % reported three or more symptoms. Half of the respondents (53 %) complained of fatigue, 43 % of dyspnoea, 27 % of joint pain and 22 % of chest pain [8]. In another study conducted by King’s College London, the UK Covid-19 Symptom Study App assessed the long-term effects of the disease [9]. One in ten users reported persistent symptoms even after three weeks. Symptoms included fatigue, headache, cough, loss of smell, sore throat, delirium and chest pain.

Due to suspected long-term consequences of COVID-19, the literature provides recommendations for physiotherapeutic treatment and early rehabilitation [10, 11] and calls for scientific studies on the topic of rehabilitation with COVID-19 [12]. Social reintegration after coronavirus disease should be of particular importance in the post-acute phase [13] as well as for patients with a mild disease course but long-lasting symptoms. Therefore, a multi-professional and interdisciplinary rehabilitation approach is recommended for moderate and severe disease progression [14, 15]. According to recent publications, there is a consensus that multimodal and interdisciplinary pneumological rehabilitation can be described as an effective therapeutic approach [14]. It is necessary to analyse the pulmonary, physical, psychosocial and cognitive dimensions of the disease within scientific studies [16] and to identify individual rehabilitation strategies based on this analysis [12].

Case reports in social networks and on public television show that the long-term effects of COVID-19 will have to be scientifically investigated in the future. These reports also demonstrate that persistent symptoms can also diverge from a linear course and vary in intensity and impairment over time. As a result, on the one hand, persons with a severe course of the disease can be found in the context of follow-up rehabilitation. On the other hand, patients with mild or moderate disease progression are impaired by long-lasting symptoms and can improve their occupational and social participation disorder through rehabilitation.

Given the novelty of the disease, there is no uniform approach to medical rehabilitation after COVID-19. Neither the rehabilitation content nor outcomes are known. In addition, the aftercare that is offered, recommended and received is also unknown. This observational study will provide recommendations for action, include a comparison group and consider the severity of COVID-19.

### Aims

The aim of our study is to describe the health status after COVID-19 in the context of medical rehabilitation and its medium- and long-term effects in different dimensions. For this purpose, the study examines the burden of disease and changes in health status under medical rehabilitation and after six and twelve months. Based on the experience of studies on pneumological rehabilitation, we expect positive effects on the general state of health and psychomental disorders at the end of rehabilitation. At follow-up, we expect that in addition to the outcomes already mentioned, rehabilitation success is represented in the dimensions of participation, quality of life, performance in various areas of life, ability to work, and subjective prognosis of employment.

Including rehabilitants from different clinics, it is possible to describe different therapeutic approaches, groups of patients and courses of disease. Statements are made about the extent to which existing rehabilitation approaches meet the needs of COVID-19 rehabilitants, the extent to which new rehabilitation therapy concepts have to be developed and how these are constituted. To date, it is unclear which requirements rehabilitants have with regard to aftercare, which recommendations rehabilitation clinics make and to what extent rehabilitants implement them.

The analyses also considered the severity of the disease course and compared the study results with a reference group with obstructive airway disease (COPD or bronchial asthma). Finally, the study will provide concrete recommendations for rehabilitation after COVID-19.

### Intervention

As an observational study, there is no intervention in the strict sense. The rehabilitants receive medical rehabilitation directly following hospitalisation or with greater time after SARS-CoV-2 infection. The duration of rehabilitation is 21 days with the possibility of extension. Given that the study participants are recruited from different clinics, the rehabilitation programmes differ in terms of therapy concept and structure.

At the MEDIAN Klinik Heiligendamm, the therapeutic elements of rehabilitation include general strengthening, mobilisation and normalisation of respiratory functions. This is intended to improve respiratory distress, respiratory muscle strength, pulmonary resilience, psychomental impairments and/or stress-induced mental disorders of the disease. The main components of the therapy include respiratory gymnastics with respiratory muscle training as well as dissolving phlegm. If required, group discussions (1–2 h per week) are offered to exchange experiences of coronavirus disease, relaxation training and supportive psychological counselling to cope with trauma, fear or depression.

The Reha-Zenrtum Schömberg treats patients in the pneumology department after severe respiratory insufficiency caused by a respiratory disease (including bronchial asthma and COPD) and after pneumonia. With this experience, the rehabilitation centre also receives COVID-19 patients for rehabilitation. The therapy contents include physical and balneotherapy, physiotherapy and exercise therapy, occupational therapy and psychological support.

Ostseeklinik Schönberg-Holm offers medical rehabilitation for various respiratory diseases. These illnesses range from bronchial asthma and COPD to the novel disease COVID-19. This facility also pursues a multimodal and holistic treatment approach during pneumological rehabilitation.

The comparison group is recruited in the MEDIAN Klinik Flechtingen and MEDIAN Klinik Flachsheide Bad Salzuflen as well as in the Ostseeklinik Schönberg-Holm and Reha-Zentrum Schömberg. The CG consists of COPD and asthma bronchial patients. These patients receive rehabilitation and aftercare according to the standards of the German Pension Insurance. The rehabilitants receive treatments comparable to those after COVID-19. Depending on their needs, the rehabilitation includes physical training (respiratory gymnastics, functional gymnastics, ergometer training, walking training, weight training, and treadmill training), respiratory physiotherapy, respiratory therapy, education, psychological interventions, nutritional therapy, counselling by social services and inhalation.

The particular therapeutic approaches are documented and described within the study.

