### Data monitoring

#### Data monitoring in the clinics is not planned

##### Case number calculation/sample size

To determine an appropriate sample size, it is assumed that the indicators used to characterise the sample should be described with sufficient precision. Sufficient precision should be applied to continuous indicators if the range of the 95 % confidence interval around a sample mean does not exceed a pre-specified value. For categorical variables, it is analogously assumed that the range of the 95 % confidence interval should not exceed a pre-specified value by a sample proportion. In the case of a continuous variable, the limits mentioned are set at +/- 5 points for a scale with a value range of 0 to 100. In the case of proportions, the range of the 95 % confidence interval should not exceed +/- 10 % points in the range of percentages from 10 to 40 %. The required width of the 95 % confidence interval is achieved with a continuous variable from a sample size of N = 100. In the case of a binary variable in the range between 10 and 40 %, the width of the 95 % confidence interval will be less than 20 % points for sample sizes of 100 or more. To compensate for smaller deviations in the required number of cases, a 20 % larger sample is taken compared to this net number of cases, i.e., N = 120 cases. We also expect a dropout rate of 20 % [37, 38]. Thus, the MEDIAN Klinik Heiligendamm will recruit N = 150, and the Reha-Zentrum Schömberg and the Ostseeklinik Schönberg-Holm will separately recruit N = 100 COVID-19 rehabilitants. For the CG, the MEDIAN Klinik Flechtingen and Bad Salzuflen will recruit N = 75 rehabilitation patients, separately, and the Reha-Zentrum Schömberg and Ostseeklinik Schönberg-Holm will recruit N = 40 rehabilitants per clinic.

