### Statistical methods

#### Quantitative analysis

In the course of the study, no predefined hypotheses are confirmed. Rather, the rehabilitation groups are precisely characterised. Comparative analyses are used to determine the relevant differences between the subgroups and the comparison group. Accordingly, we mainly provide descriptive evaluations on the burden of disease as well as on health-related changes during and after rehabilitation.

For the interval-scaled variables, variance analyses with measurement repetition are calculated to evaluate the pre-post differences of the outcomes at the various measurement times. Depending on the data constellation, the t-test for dependent or independent samples is used as a parametric significance test. Non-parametric tests are performed for ordinally scaled data. Subgroup analyses will be planned for sex, age and education as well as risk factors and comorbidities. To classify the findings in COVID-19 patients, the stress manifestations and the measured changes are compared with those in the CG.

In addition to the analysis of the health-related changes in relation to a comparison group, the treatment concepts from different rehabilitation facilities are also examined. The type and extent of the therapy, characteristics of the included rehabilitants, perceived benefits of the rehabilitation and subjectively experienced health improvements are recorded. All calculations are performed with SPSS 22.0.

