### Limitations

To ensure equal treatment, all characteristics of the participants (e.g., age, education) and the disease (e.g., severity of the disease, disease status, and comorbidity) are documented and compared between groups. If differences arise between the two groups, they are comparably integrated in the analysis (e.g., as covariates in multivariate methods or by propensity score matching). Based on our present knowledge, we assume that structural changes in the context of this project are very unlikely.

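### The COVID-19 versus comparison-group contrast is partly a contrast of clinics, and the stated adjustment rule does not cover clinic

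*Protocol article*

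**What the plan says.** All references are to the protocol article.

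- **Sample (Abstract, Methods):** "The study sample will consist of *N* = 350 rehabilitants after COVID-19 and a comparison group (CG) with *N* = 230 rehabilitants".
- **Where each group comes from (Case number calculation/sample size):** for COVID-19, "the MEDIAN Klinik Heiligendamm will recruit N = 150" and "the Reha-Zentrum Schömberg and the Ostseeklinik Schönberg-Holm will separately recruit N = 100 COVID-19 rehabilitants". For the comparison group (CG), "the MEDIAN Klinik Flechtingen and Bad Salzuflen will recruit N = 75 rehabilitation patients, separately", and Schömberg and Schönberg-Holm add 40 each. The Intervention section agrees: "The comparison group is recruited in the MEDIAN Klinik Flechtingen and MEDIAN Klinik Flachsheide Bad Salzuflen", followed by the same two shared clinics. Heiligendamm is not among the CG clinics.
- **Clinics differ (Intervention):** because several clinics recruit, "the rehabilitation programmes differ in terms of therapy concept and structure". The same section later calls the CG's treatment comparable to that given after COVID-19, without supporting detail.
- **The comparison (Quantitative analysis):** to put the COVID-19 findings in context, "the stress manifestations and the measured changes are compared with those in the CG". Repeated-measures variance analyses, t-tests and non-parametric tests are listed. Treatment concepts of the facilities are examined in addition to this comparison.
- **Adjustment (Limitations):** the rule covers "all characteristics of the participants (e.g., age, education) and the disease". Where the groups differ, these characteristics enter as covariates or through propensity score matching. Clinic is not named.

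**The concern.** Clinic is tied to group by the recruitment plan itself. A COVID-19 rehabilitant has a 43% chance of coming from a clinic with no CG patients, and a CG patient a 65% chance of coming from a clinic with no COVID-19 patients. Anything that differs between those clinics, such as programme, referral pattern or the way rehabilitation is delivered and rated, appears in the group difference.

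The stated adjustment cannot undo this. Matching on age, education, severity or comorbidity may pair a Heiligendamm COVID-19 rehabilitant with a Flechtingen CG patient. Their measured characteristics then agree, and the clinic difference stays intact. Recruiting more patients at the same clinics would not reduce this error either.

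At stake is the reading of the comparison. The article uses the CG to classify the COVID-19 findings and to draw conclusions on rehabilitation and aftercare. A difference in change scores could be put down to disease group when part of it belongs to the clinics.

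**Working it through.** **1. Reproduce the plan's totals** (quotas from Case number calculation/sample size).

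| Clinic | COVID-19 | CG |
|---|---|---|
| Heiligendamm | 150 | 0 |
| Schömberg | 100 | 40 |
| Schönberg-Holm | 100 | 40 |
| Flechtingen | 0 | 75 |
| Bad Salzuflen | 0 | 75 |
| Total | 350 | 230 |

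Both totals match the Abstract. Single-group clinics hold 150/350 = 42.9% of COVID-19, 150/230 = 65.2% of CG, and 300/580 = 51.7% of all participants.

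**2. Weight of each clinic in an unadjusted difference of group means.** Weight = (its share of COVID-19) − (its share of CG).

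- Heiligendamm: 150/350 = +0.429
- Schömberg and Schönberg-Holm: 100/350 − 40/230 = +0.112 each
- Flechtingen and Bad Salzuflen: −75/230 = −0.326 each

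A shift of one unit specific to Heiligendamm thus moves the overall difference by 0.43 units. The sum of squared weights is 0.421 and its root is 0.649. Clinic effects therefore enter with an SD of 0.65 times the between-clinic SD.

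**3. Size in outcome SD units.** The ICC is not in the documents, so 0.01 to 0.10 is an assumption. The between-clinic SD is √ICC, and the clinic error is 0.649 × √ICC.

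| Assumed ICC | Clinic error (SD) |
|---|---|
| 0.01 | 0.065 |
| 0.02 | 0.092 |
| 0.05 | 0.145 |
| 0.10 | 0.205 |

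**4. Sampling error for scale.**

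- As recruited: √(1/350 + 1/230) = 0.085.
- After the plan's 20% dropout (280 vs 184): √(1/280 + 1/184) = 0.095.

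At an ICC of about 0.02 the clinic error is already about as large as the sampling error. The figure without dropout is the relevant one for the baseline comparison.

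**5. What clinic adjustment leaves.** With clinic as a fixed factor, only clinics with both groups inform the group contrast: Schömberg and Schönberg-Holm, 200 vs 80 recruited (280 of 580), or 160 vs 64 after dropout. Dropout is taken as equal across clinics.

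- Standard error as recruited: √(1/200 + 1/80) = 0.132, against 0.085.
- After dropout: √(1/160 + 1/64) = 0.148, against 0.095. The ratio is 1.56 and the variance ratio 2.43.
- 95% half-width after dropout: 1.96 × 0.148 = 0.29 SD, against 1.96 × 0.095 = 0.19 SD.

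**The case against.** The study is exploratory and mainly descriptive, and it confirms no predefined hypothesis. Its sample size rests on the precision of single means and proportions, not on a group contrast. The CG is meant to be similar in age, sex and ability to work, measured case-mix differences are to be adjusted for, and facilities are examined in their own right. Clinic is coded in the participant ID, so no information is lost. A fuller plan may contain a clinic term. These points lower the weight of the issue and answer the part of it that is measured case mix.

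They do not answer the rest. The article states an adjustment rule. Its lists of examples are open, but only within participant and disease characteristics, and clinic is neither. The facility analysis stands beside the group comparison, not inside it. Significance tests are planned, and the Limitations section does not mention the recruitment pattern.

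Three stronger readings are tempting and not supported:

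- **That the plan fixes a pooled, unadjusted test whose 95% intervals cover far too little.** The article never says pooled, and it allows covariates or matching. Any coverage figure would apply only to a crude contrast and would follow from whichever ICC is assumed. The same model treats five named clinics as random draws and uses one ICC for both burden and change.
- **That group and clinic cannot be separated.** Two clinics recruit both groups, so a within-clinic contrast exists.
- **That the study's main results are compromised.** Description of COVID-19 rehabilitants and of their change over time does not use the CG.

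**Conclusion.** The point holds as partial confounding of group with clinic that the stated adjustment rule does not reach. The recruitment pattern and the wording of the rule are in the text and need no assumption. The size does: between 0.065 and 0.205 outcome SD for an unadjusted contrast if the ICC lies between 0.01 and 0.10, which is from below to more than twice the sampling standard error. Adjustment for patient factors would remove whatever part of this is measured case mix and leave the part due to programme and referral.

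In an exploratory study this is a weakness in one comparison and its interpretation. It is worth correcting before analysis but does not threaten the study as a whole.

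**What to change.** - **Quantitative analysis:** keep the overall COVID-19 versus CG contrast. Beside it, report the clinic-adjusted contrast with its confidence interval as a sensitivity analysis, and say that it is in effect the within-clinic contrast from Schömberg and Schönberg-Holm. For change over time in a repeated-measures model, adjustment needs a clinic-by-time term (or clinic in a model of the change score), since a clinic main effect removes only differences in level.
- **Limitations:** state that three of five clinics recruit one group only, that the overall contrast is therefore partly confounded with clinic, and that it should not be attributed to disease group alone.
- **Intervention:** reconcile the statement that programmes differ between clinics with the statement that CG treatment is comparable.

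No rule should require the two contrasts to agree before a difference is reported. The shared-clinic estimate is too imprecise for that, and showing both intervals is enough.

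**Cost:** no new data, since clinic is already in the ID. The adjusted contrast uses 280 of 580 participants, with about 64 CG patients after dropout, and its standard error is about 56% larger (0.148 vs 0.095 SD). At an assumed SD of 25 points on a 0 to 100 scale, that is about ±7.2 instead of ±4.7 points. It also speaks for two clinics only.

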## Methods

### Eligibility criteria

Rehabilitants after varying degrees of COVID-19 who are able to work will be recruited to the study. The rehabilitants may no longer remain in isolation. Participants are between 18 and 65 years old and provide written consent. Participants in the control group have a diagnosis of obstructive airway disease, such as bronchial asthma or COPD. This group will be similar based on age, sex and ability to work.

Individuals who do not provide consent and who do not have sufficient knowledge of German are excluded. Furthermore, rehabilitation may not be paid by German Social Accident Insurance.

